### Clinical evaluations

The main morbidity outcome will be incidence of clinical disease assessed by PCD; data from this will provide the primary endpoint of the study. Mild malaria and parasitaemia is common in all children in this area of highly seasonal malaria [21-23]. Study nurses in the 6 health facilities (Tiefora, Koflandé, Boussara Brousse, Madiasso, Soukara II and Kangounadeni) within the study area will document episodes of malaria in study children who present directly to them. At the health facilities malaria diagnosis will rely on the use of RDT but, in addition, thick blood films will be made for Giemsa staining and later microscopy to estimate parasite density. To facilitate documentation of all consultations by study children, all enrolled children will be issued with enumerated photo identity cards. The child’s study number, initials and village code will be recorded for all clinical events on the case report form (CRF); to maintain confidentiality the initials will not be entered into the data set.

During the surveys all children enrolled in the cohort who are present and the randomly selected children for the cross-sectional surveys will be clinically examined for obvious symptoms and signs of illness, temperature will be measured with calibrated digital thermometers and spleen enlargement will be measured by experienced nurses using Hackett’s scoring system. All children will be finger pricked for immediate measurement of anaemia using a spectrophotometer (HaemoCue®, Ängelholm, Sweden) and preparation of thick smears. If a child reports with fever in the last 48 hours and/or with a temperature ≥37.5 °C they will also be checked for presence of parasites by RDT.

The primary endpoint selected is the definition of malaria used commonly in West Africa in research studies and in National Treatment Guidelines [24-26]. This endpoint does not include a measure of parasite density and a parasite cut-off level may increase specificity. We thus also intend to use the logistic regression method of Smith and colleagues [26] to examine the effect of parasite cut-off on the specificity and sensitivity of the definition of clinical malaria. This method has been endorsed by a WHO study group for use in studies defining malaria vaccine efficacy [21].

### Entomological evaluations

Exposure to mosquitoes will be measured by surveillance with light traps to obtain the primary entomological endpoint [27]. A CDC miniature light trap will be positioned close to a single sleeper protected with a LLIN or PPF-LLIN. Mosquitoes will be identified by microscopy and the numbers of *An. gambiae* s.l., *An. funestus* and other anophelines recorded. The presence of sporozoites in *An. gambiae* s.l. will be identified using an enzyme-linked immunosorbent assay [28] and *An. gambiae* s.l. females will be typed to species by PCR [29]. In the case of *An. gambiae s.s.*, S and M forms will be identified by PCR [30]. Published kdr resistant markers will be typed by PCR [31,32].

6 sentinel clusters will be selected for measurement of the secondary entomological endpoints. Larvae will be collected from a range of breeding sites within each of these sites at the beginning and end of the transmission season in each year of the study. The prevalence of resistance to pyrethroids will be measured using standard diagnostic dose assays with papers impregnated with permethrin, obtained from WHO [33]. To quantify the strength of resistance, a modification of the CDC bottle bioassay will be used in which 3- to 5-day old non-blood-fed female mosquitoes are introduced into 250 mL glass bottles pre-coated with a range of permethrin concentrations. After a 1 hour exposure the mosquitoes are transferred to a holding tube, provided with sugar and water, and mortality recorded 24 hours later. The concentration required to obtain 50% mortality, 24 hours post-exposure is recorded.

To assess the impact of PPF-LLIN on *Anopheles gambiae* egg production and the survival of the larvae that emerge from these eggs, blood-fed mosquitoes will be collected from inside houses via manual aspiration or when exiting houses using exit traps. The female mosquitoes will be transported to the local insectary at Banfora and the number of females that lay eggs, number of eggs hatching and survival to L2 larval stages will be recorded. This will be performed in all 6 sentinel clusters at the beginning and end of the transmission season in each year. In the first round of monitoring, all houses will have standard LLINs and at the final round of monitoring all will have PPF-LLIN.

### Study procedures and evaluations

LLIN distribution will be completed in mid-2014. Study nurses and field assistants will be provided with refresher training on diagnosis of malaria, the use of RDT and study procedures in 2014 and 2015 before the transmission season.

The compound of each study child will be geo-referenced using a hand-held global positioning system, as the primary data analysis has a spatial component. Travel/residence of cohort children will be assessed at monthly intervals on brief questionnaires to estimate their time at risk, and their bed net usage will be assessed at the same time.

Thick blood films will be stained with Giemsa and examined under 1000-fold magnification by trained, experienced microscopists. Parasite counts will be recorded per high power field and 100 fields will be counted before a slide is declared negative. Parasite density will be estimated assuming that one parasite per high power field equals 500 parasites/μL [34]. 2 slides will be prepared from each subject and read separately by 2 experienced microscopists; discrepancies in positive and negative reads and those greater than 10-fold between the 2 reads will be resolved by the microscopy supervisor. Field staff will deliver all CRF to the study physician within 2 days of the clinical attack or survey date. The study physician will check all CRFs weekly for completion and data consistency.

### Safety considerations

Although adverse events (AEs) arising from either net are highly unlikely, we will document their safety in a community setting, by recording AEs and serious adverse events (SAEs) in the study cohort and population for the duration of the study. The trial will follow standard definitions for AE and SAE agreed by consensus of the Collaborating Centres of the WHO International Drug Monitoring Centre (Uppsala, Sweden). The occurrence of AEs will be sought by non-directive questioning of the study children at monthly visits during the trial. AEs will also be recorded if volunteered by study children or their parent/carer or are noted by nurses through physical examination, laboratory test, or other assessments at any contact with the participant; these will be recorded on the child’s CRF for that visit. All AEs such as skin rashes, respiratory problems, streaming eyes, and so forth, will be recorded with the grade of severity (mild, moderate or severe).

In addition, we will record pregnancy outcomes for all resident pregnant women, and asthma signs/symptoms in pre-identified asthmatic residents, as indicated in the clinical data collection and patient treatments above.

During the course of the study, SAEs will be captured using a specific SAE report form and within 2 days of the start of the SAE, field staff will deliver a completed SAE report to the study physician. The study physician will log these in a query book noting the child’s study identification number or the residents demographic surveillance system number and village of residence and report these to the Principle Investigator who will inform the responsible member of the trial Data and Safety Monitoring Committee. Excessive grouping of SAEs by clusters will be reported to the study’s Data Monitoring and Ethics Committee and Trial Steering Committee.

### Handling of drop-outs/withdrawals

If an individual wants to terminate his/her participation, no further follow-up will be performed. There will be no replacement during the surveillance period in either year but in May 2015 children who have withdrawn, or are no longer in the study for whatever reason, will be replaced by children resident in the same cluster and of the same age group if informed consent is provided. If a household withdraws consent, no further follow-up will be made in that household. A child who was participating from that household will be replaced from within the same cluster and age group and, if the house was participating in the entomology collections, it will be replaced by a neighbouring house of the same type if possible. If a village opts out of the study before July in either year replacement by a neighbouring village will be considered.

### Study endpoints

#### Clinical

Primary: incidence of clinical episodes of malaria presenting at health facilities defined as a child with an axillary temperature ≥37.5°C or a history of fever in the past 48 hours, together with the presence of *P. falciparum* parasites of any density detected by RDT in the absence of other detectable cause of fever.

Secondary: (i) mean Hb concentration in children in the 2 study arms measured at the end of the transmission season survey; (ii) *P. falciparum* parasite rates in children in the 2 study arms measured at the end of the transmission season.

In addition we will also reportthe incidence of malaria defined by history of fever or temperature ≥37.5 °C and a *P. falciparum* parasitaemia cut-off to give optimum sensitivity and specificity in this settingthe number of children with enlarged spleens at the end of each transmission season.

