Polyethylene nets treated with a combination of permethrin and pyriproxyfen (PPF-LLIN; trade name Olyset Duo (Sumitomo Chemical, Japan),) have been shown to induce higher mortality and reduce blood feeding of pyrethroid-resistant *Anopheles gambiae* s.s. than permethrin-only LLINs (Olyset) in experimental hut trials [11]. However, no controlled study demonstrates that PPF-LLIN will provide incremental protection against malaria beyond the current best practice of LLIN and prompt treatment in a controlled trial. Building on current best practice, the present trial aims to measure the incremental impact of PPF-LLIN on clinical malaria in communities using LLINs alone and having access to rapid treatment. To achieve this we will conduct a cluster randomised controlled trial in rural villages to the south-east of Banfora town in Burkina Faso, a country where malaria is relatively stable [18]. Mosquitoes in this area are currently increasing in resistance to pyrethroids. In 2010 in Tiefora, located at the edge of our trial zone, there was resistance to 1,1,1-trichloro-2,2-di(4-chlorophenyl) ethane (DDT) (12% mortality), permethrin (48% mortality) and deltamethrin (39% mortality) ([name], personnel communication).

Here we describe the proposed trial design and the methodology used. Although some of the outcome measurements and methods in this protocol are based on a previous vector control trial conducted in West Africa [19], the nature of the intervention and setting have led to many novel features.

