### Design

A cluster-randomised controlled trial design will be used since: i) LLINs are a community-level intervention; and ii) the village cluster is a suitable unit for randomization since they represent a discrete spatial cluster. At the outset of the study, all households will be provided with new LLINs at the rate of 1.1 nets for every 2 people in their household; this will approximate 1 for every sleeping place. Each month for the next 4 months after LLIN donation, residents in 5 randomly selected village clusters will be asked to exchange their LLINs for PPF-LLIN. Stratified, random sampling will be used to ensure that by the end of year 1 (September 2014) there will be a similar number of residents with and without PPF-LLINs affiliated to each health centre. Every month from June to September in 2015, an additional 5 village clusters will be provided with PPF-LLIN, thus by the end of September 2015 all clusters will have PPF-LLIN (Figure 1). It is important that within the study area there are no villages that are not enrolled in the study in order for the PPF-LLIN to have maximum impact on larval populations and minimize the spill-over of mosquitoes from villages without these nets. LLINs and PPF-LLIN will be the same shape, size and colour and marked with a unique code number, so that the investigators are blinded to the identity of the net (apart from those field assistants distributing nets).

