### Clinical data collection and patient treatments

PCD for malaria will be maintained during the transmission seasons in 2014 and 2015 (June to December 2014, and June to December 2015). Parents/guardians will be encouraged to take their child to the health facility their village is affiliated with at any time their child becomes unwell. The cost of travel and treatment for sick children will be met from the study funds. Study nurses will work in close collaboration with the government health workers to monitor malaria cases as indicated above. Project fieldworkers will visit each nurse regularly, at least once a week, to record children with malaria episodes.

The end of transmission season survey in December 2015 will be the final study visit for the enrolled children in the cohort and will be similar to the end transmission season survey in 2014.

During the course of the study participants are free to receive medication from health personnel outside the study team but they are encouraged to use their allocated health facility. During the clinical surveys, sick children, those with anaemia (haemoglobin (Hb) <9 g/dL), diagnosed malaria or any other mild illness will be referred to their health facility. Children with severe malaria, or other serious conditions, will be referred to Banfora or Sideradougou Health Centres for treatment.

For safety considerations (see section below) we will identify asthmatic residents in study villages by name, household and village. During distribution and follow-up of PPF-LLIN in 2014 and 2015 these residents will be checked weekly by trial nurses for any aggravation of their symptoms for the first month after net donation and at the end of this month they will ask these residents to contact the study team if they have cause for concern. We will also identify pregnant women in study villages from antenatal clinic records, from June 2014 onwards, and outcomes of pregnancies will be recorded onto data forms, including miscarriages, live/still birth, weight and any recorded malformations. The regular monthly demographic surveillance system (DSS) in trial villages will also include reports of miscarriages. Data on asthmatics and pregnancy outcomes will then be linked to the date of reception of PPF-LLIN to examine if the events are associated with PPF-LLIN.

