#### Secondary endpoints

For the secondary clinical endpoints we will compare: (i) mean Hb concentration in children at the end of the transmission seasons; (ii) incidence of malaria defined by history of fever or temperature ≥37.5 °C and a *P. falciparum* parasitaemia cut-off defined to give optimum sensitivity and specificity in this setting; (iii) parasite rates (sexual and asexual) in children at the end of the transmission seasons; (iv) number of children with enlarged spleens at the end of the transmission seasons; and (v) prevalence of anaemia (mild, moderate, severe). Anaemic statuses will be defined as: severe anaemia = Hb <5 g/dL, moderate anaemia = Hb range from 5 to <8 g/dL and mild anaemia = Hb range from 8 to <11 g/dL.

In general, all quantitative outcomes will be compared using appropriate summary statistics, such as mean differences or risk ratios. Hypothesis testing will be based on a 2-sample unpaired *t* test, adjusting for possible co-variates. If the data do not satisfy normality and constant variance assumptions, an appropriate non-parametric test will be applied. Both linear regression (for continuous variables such as Hb levels) and logistic regression (for dichotomous variables such as presence or absence of parasitaemia) will be used to quantify the group differences allowing for individual level covariates (such as age, house design, bed net use) using covariance structures that represent the appropriate level of clustering.

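### The December 2015 survey and the final sentinel entomology round have no concurrent LLIN arm, yet the secondary endpoints are defined as arm comparisons with no named term for calendar time

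*Protocol article*

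**What the plan says.** **Roll-out.** Under Design, each month for four months in 2014, "residents in 5 randomly selected village clusters will be asked to exchange their LLINs for PPF-LLIN". In the second year, "Every month from June to September in 2015, an additional 5 village clusters will be provided with PPF-LLIN", and "thus by the end of September 2015 all clusters will have PPF-LLIN". The Abstract agrees: full coverage comes three months before the trial ends.

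**Surveys.** Design places cohort surveys at the start and end of both seasons. Clinical data collection and patient treatments says: "The end of transmission season survey in December 2015 will be the final study visit for the enrolled children".

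**Secondary clinical endpoints.** Study endpoints, Clinical, gives "Secondary: (i) mean Hb concentration in children in the 2 study arms measured at the end of the transmission season survey", and parasite rate in the same two-arm form. The Secondary endpoints part of the Analytical plan uses the plural, "mean Hb concentration in children at the end of the transmission seasons", applies the same timing to parasite rates and spleen enlargement, and adds anaemia prevalence. It bases hypothesis testing on a two-sample unpaired t test with covariate adjustment. The covariates it gives as examples are age, house design and bed net use.

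**Secondary entomological endpoints.** Study endpoints, Entomological, defines change in permethrin resistance in each arm over the study, and fertility and fecundity in both arms. These come from six sentinel clusters, sampled at the start and end of each season. Entomological evaluations states: "In the first round of monitoring, all houses will have standard LLINs and at the final round of monitoring all will have PPF-LLIN". The Background adds: "Mosquitoes in this area are currently increasing in resistance to pyrethroids".

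**The concern.** The endpoint definitions presuppose two arms at each end-of-season survey, but the roll-out leaves only one by the second. The arm comparison in December 2015 cannot be made at all. If that survey is combined with December 2014, every LLIN observation comes from 2014 and most PPF-LLIN observations come from 2015. A difference between the two malaria years would then appear as a net effect unless the analysis separates time from net type.

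The sentinel endpoints are exposed in the same way. Resistance is stated to be rising already, so a comparison of the all-LLIN first round with the all-PPF-LLIN final round cannot separate the net from the trend.

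At stake is what the trial can conclude on haemoglobin, parasite rate, anaemia, spleen enlargement, mosquito fertility and resistance.

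**Working it through.** **1. Net split by date.** Five clusters a month for four months gives 4 × 5 = 20 in 2014, and the same again in June to September 2015 gives 40.

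| Time | PPF-LLIN clusters | LLIN clusters |
|---|---|---|
| September to December 2014 | 20 | 20 |
| June 2015 | 25 | 15 |
| July 2015 | 30 | 10 |
| August 2015 | 35 | 5 |
| September to December 2015 | 40 | 0 |

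The start-of-season survey in 2015 would also be 20 versus 20 if it is held in May, before the June exchanges. That date is inferred from the May 2014 baseline and the May 2015 replacement of drop-outs. The endpoint definitions use end-of-season surveys only.

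**2. The plan's own sample size.** The check uses the unmatched cluster formula c = 1 + (z₀.₉₇₅ + z_power)² × [sampling variance + k²(m₀² + m₁²)] / (m₀ − m₁)², with a two-sided 5% level.

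- Primary endpoint: 1.5 versus 1.125 episodes, k = 0.25, 50 children × 2 seasons = 100 child-years per cluster, 90% power. c = 1 + 10.507 × (0.02625 + 0.21973)/0.140625 = 19.38, as stated.
- Prevalence: 30% versus 21%, k = 0.3, 45 children per cluster, 80% power. c = 1 + 7.849 × (0.00835 + 0.01207)/0.0081 = 20.8. With 20 per arm the power is 78.4%, close to the stated 80%.

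The prevalence calculation needs 20 clusters in each arm. Of the two end-of-season surveys, only December 2014 supplies them.

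**3. Simple pooling of both Decembers.** This would set 20 + 40 = 60 PPF-LLIN cluster-surveys against 20 LLIN cluster-surveys, all of the latter from 2014. Let r be the 2015/2014 prevalence ratio. The documents give no value for r, so the values below are assumptions. With no net effect, the apparent ratio is (20 × 1 + 40 × r)/60.

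| Assumed r | Apparent PPF-LLIN/LLIN ratio |
|---|---|
| 0.7 | 48/60 = 0.80 |
| 0.8 | 52/60 = 0.87 |
| 1.3 | 72/60 = 1.20 |

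The planned detectable ratio is 21%/30% = 0.70. At r = 0.7 the change of year alone yields a 20% apparent reduction, two-thirds of the 30% target.

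**4. Value of December 2015 in a model with round effects.** The stepped-wedge variance formula was applied with illustrative inputs: prevalence 0.255, k = 0.3, 45 children per cluster, a constant net effect and stable cluster effects. The standard error of the prevalence difference is 0.032 from December 2014 alone and 0.026 with both Decembers. From December 2015 alone the effect is not estimable. The later survey adds information on cluster effects, but only in a model that an unpaired t test does not provide.

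**5. Named adjusters.** Outcome 1 of the Analytical plan lists clustering, distance to the nearest LLIN cluster, time of use of current nets, cluster size, sex, house design and bed net use. Time of use runs from the exchange and is not calendar time. Only the catch-all for other confounders could take in year or survey round.

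**6. Sentinel rounds.** Of the four rounds, the first is all LLIN and the last all PPF-LLIN. Net types can be concurrent only at end 2014 and start 2015, and only if the six clusters include both roll-out years. The article does not say that they do.

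**The case against.** A stepped wedge ends with every cluster on the intervention, and the protocol describes and justifies this openly. Outcome 1 promises multi-level models for every outcome measure, with adjustment for other relevant confounders. The endpoint definition uses the singular for the end-of-season survey, which December 2014 satisfies. The choice of rounds and time terms is often left to an analysis plan, and that plan is not shown.

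Much of this stands, and it rules out several stronger readings that a reader might infer:

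- *That the protocol plans crude 60 versus 20 pooling.* It nowhere says so. The ratios above show what omitting a time term could do; they are not the bias of a stated analysis.
- *That first-versus-final is the planned sentinel contrast.* The protocol states the net status at those rounds but does not name the contrast.
- *That the secondary endpoints are lost or the sample size is wrong.* December 2014 gives the powered 20 versus 20.
- *That the December 2015 data are useless.* In a model with round effects they add precision.
- *That the primary results are undermined.* Clinical incidence and EIR are collected through both seasons and keep concurrent LLIN clusters until the last 2015 step.

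What does not stand is that the matter is merely left open. The article itself fixes the plural timing, the two-arm form and the unpaired t test for the secondary endpoints, and those three do not fit its own roll-out. The outside comparison that Design offers for changes between years, health-facility records, covers clinical malaria only. It supplies no comparator for haemoglobin, parasite rate, spleen enlargement or the sentinel measures.

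**Conclusion.** The point holds for the survey-based secondary clinical endpoints and the sentinel entomological endpoints. As written, the arm comparison is not estimable in December 2015, and combining the two Decembers without a time term confounds net type with year. The counts (20 versus 20, then 40 versus 0) follow directly from the protocol. The illustrative range of 0.80 to 1.20 rests on assumed year ratios of 0.7 to 1.3, no net effect and simple pooling. The precision gain from December 2015 rests on a constant net effect, whereas the Discussion expects the effect to grow with coverage. That is a further reason to report the December 2014 contrast in its own right.

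**What to change.** - **Survey endpoints.** Replace the unpaired t test with a mixed model that has survey-round fixed effects and cluster random effects, keeps the December 2015 data, and classifies each cluster by the net it holds at that survey. Name the December 2014 comparison (20 versus 20) as the directly randomised concurrent end-of-season contrast. Make no stand-alone arm comparison for December 2015.
- **Sentinel endpoints.** Balance the six clusters between the 2014 and 2015 roll-outs (three and three). Base arm contrasts on the end-2014 and start-2015 rounds, or on a model with round effects. Label any first-versus-final comparison as before-after.

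The cost is revised endpoint and analysis wording and a stratified choice of sentinel clusters. The downside is that the concurrent randomised contrast covers less than two full seasons of PPF-LLIN use. By December 2014 the 2014 clusters have had the nets for about three to six months (exchanges from June to September 2014), and by May 2015 for at most about 11 months. A three-versus-three sentinel contrast will also be imprecise and should be reported as such.
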